## Abstract

**Background:**

Patients presenting with the coronavirus-2019 disease (COVID-19) may have a high risk of cardiovascular adverse events, including death from cardiovascular causes. The long-term cardiovascular outcomes of these patients are entirely unknown. We aim to perform a registry of patients who have undergone a diagnostic nasopharyngeal swab for SARS-CoV-2 and to determine their long-term cardiovascular outcomes.

**Study and design:**

This is a multicenter, observational, retrospective registry to be conducted at 17 centers in Spain and Italy (ClinicalTrials.gov number: NCT04359927). Consecutive patients older than 18 years, who underwent a real-time reverse transcriptase-polymerase chain reaction (RT-PCR) for SARS-CoV2 in the participating institutions, will be included since March 2020, to August 2020. Patients will be classified into two groups, according to the results of the RT-PCR: COVID-19 positive or negative. The primary outcome will be cardiovascular mortality at 1 year. The secondary outcomes will be acute myocardial infarction, stroke, heart failure hospitalization, pulmonary embolism, and serious cardiac arrhythmias, at 1 year. Outcomes will be compared between the two groups. Events will be adjudicated by an independent clinical event committee.

**Conclusion:**

The results of this registry will contribute to a better understanding of the long-term cardiovascular implications of the COVID19.

## Introduction

Since Coronavirus disease 2019 (COVID-19) was first reported in China in late December 2019, it has spread rapidly worldwide, and it has become a pandemic affecting more than 200 countries. The exponential increase in the number of COVID-19 patients has overwhelmed health-care systems in many countries across the world, with an unprecedented effect not only on public health, but also on social and economic activities.

COVID-19 is caused by the severe acute respiratory syndrome coronavirus-2 (SARS-CoV-2). Currently, it is known that SARS-CoV-2 can produce a multi-system affectation, including cardiovascular system [1]. This virus enters the cells by binding of the viral spike (S) protein to angiotensin-converting enzyme 2 (ACE2) on the surface of the host cell. The ACE2 is highly expressed in pulmonary tissues, but also in adult human hearts and endothelial cells, indicating an intrinsic susceptibility of these organs to a direct invasion of SARS-CoV-2. Furthermore, SARS-CoV-2 probably produces a downregulation in the ACE2 activity, reducing the conversion of angiotensin II (Ang II) to Ang-(1–7). This may increase Ang II activity, which continues stimulating renin-angiotensin-aldosterone system (RAAS) with deleterious effects on heart and blood vessels [2–4].

An exacerbated inflammatory response with cytokine storm mediated through pathologic T cells and monocytes leading to myocarditis, is another possible mechanism postulated to explain cardiac injury due to COVID-19 [5, 6]. The pro-inflammatory environment and endothelial dysfunction can also trigger the development of coagulopathy. Hypercoagulability leads to coronary macro and microvascular thrombosis, and high incidence of thromboembolic events in venous territories [7–9].

We currently know that myocardial injury is related with worse in-hospital prognosis in COVID-19 patients [10–12]. A study of 26 patients recovered from COVID-19 evaluated with cardiac resonance showed myocardial edema, fibrosis, and impaired right ventricle function [13]. Available data suggests a probable implication on prognosis, but long-term implications of COVID-19 on cardiovascular events are completely unknown.

The Cardiovascular COVID-19 (CV COVID-19) registry will aim to a better understanding of the long-term cardiovascular implications in patients who had a SARS-CoV-2 infection.

## Methods

### Study design

It is a multicenter, observational, retrospective registry to be conducted at 17 centers in Spain and Italy. This study is an investigator-initiated registry, and the promoter is the Fundació Clínic per a la Recerca Biomédica. **Table 1** shows the list of enrolling centers and their principal investigators. The detailed list of the study staff is in the **S1 File**.

**Table 1 pone.0255263.t001:** Centers and investigators.

Centers	Investigators
Hospital Universitari Clínic de Barcelona	[name]
Hospital Universitari Sagrat Cor	[name]
Hospital Universitari de Bellvitge	[name] [name]
Hospital Marqués de Valdecilla	[name] [name]
Hospital Universitario Juan Ramón Jiménez	[name] [name], [name] [name]
Hospital Universitario La Princesa	[name]
Hospital Universitari Vall d’Hebron	[name] [name]
Hospital Clínico Universitario de Valladolid	[name] [name]
Hospital Universitario de León	[name]
Hospital Universitario de Vigo	[name] [name]
Hospital Universitario Clínico San Carlos	[name]
Istituto Clinico Sant’Ambrogio	[name]
Azienda Ospedaliero-Universitaria di Ferrara	[name]
Hospital de Tortosa Verge de la Cinta	[name]
Ospedale Bolognini di Seriate	[name]
Hospital Universitari Arnau de Vilanova	[name]
Hospital Universitari Joan XXIII	[name]

The Registry does not test clinical interventions, and individual patient care is entirely at the discretion of treating clinicians.

This study adhered to the principles outlined in the Declaration of Helsinki. Approval was given by the “Comité de Ética de la Investigación con medicamentos del Hospital Clínic de Barcelona” (Ethics Committee for Drug Research of the Hospital Clínic of Barcelona) with the registry HCB/2020/0457, on April 16, 2020. Given the registry’s anonymous characteristics and the health alarm situation generated by the COVID-19 pandemic, written informed consent was waived.

The study is registered at ClinicalTrials.gov (NCT number: NCT04359927).

### Patient selection

Inclusion criteria are:

At least 18 years of age.Patient who underwent a nasopharyngeal swab for real-time reverse transcriptase-polymerase chain reaction (RT-PCR) for SARS-CoV2 between March 2020 and August 2020.

Exclusion criteria are:

Those with terminal diseases and a life expectancy <1 year before the diagnosis will be excluded.

Patients will be classified into two groups: patients with confirmed COVID-19 (positive RT-PCRT for SARS-CoV-2) and patients without COVID-19 (negative RT-PCR for SARS-CoV2, and absence of absence of suspicious symptoms).

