### Statistical analysis plan

We did not estimate a precise sample size, due to lack of literature reports and we aim to get the maximum numbers of patients possible.

Continuous variables will be presented as mean ± standard deviation. Categorical variables will be reported as absolute number and percentage. Differences in proportions will be tested with Chi-square test or Fishers exact test and differences in continuous variables will be tested with a Student’s t-test. Kaplan-Meier method will be used to derive the event rates at follow-up and to plot time-to-event curves. Patients not eligible for 1-year follow-up will be considered at risk until the date of last contact, at which point they will be censored.

To determine the predictors of cardiovascular death, a Cox proportional hazards model will be used together with the Wald test to compare the results between the groups (patients with positive vs. negative RT-PCR for SARS-CoV-2).

All p-values will be two-sided and a value <0.05 will be considered statistically significant. All data will be processed using the Statistical Package for Social Sciences, version 22 (SPSS Inc., Chicago, IL, USA).

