## Discussion

In this multicenter, observational, retrospective registry, we aim of investigate the long-term cardiovascular implications of COVID-19. Currently is known that the presence of myocardial injury, vascular dysfunction and thrombosis in patients with COVID-19 have an important role in the short-term prognosis in these patients [9]. Previous experience with the severe acute respiratory syndrome coronavirus-1 (SARS-CoV-1) emerged in 2002, suggests that both the underlying disease and its treatment could be associated with a worse cardiovascular prognosis. In a study of 25 survivors of SARS-CoV-1, at 12 years of follow-up, altered lipid metabolism was found [17]. Similarly, viral diseases such as influenza A are associated with increased cardiovascular mortality after infection [18].

The focus of this registry will be on the cardiovascular outcomes, providing data not only about cardiac ischemic events but also arrhythmias, cerebrovascular events and heart failure. It should be highlighted that our findings will be applicable to any COVID19 patient, regardless of the severity of the disease, as we will be including a consecutive population of patients with COVID-19 infection. Confirmed cases will be evaluated and compared with those patients who did not have COVID-19 infection. This approach will offer a greater security at the moment of assessing study’s findings. This control group will help to minimize bias that would arise if only COVID-19 patients were independently analyzed. Cox regression will help to distinguish the independent predictors for mortality among the patients of the study. However, considering that a proportion of the SARS-CoV-2 infections can be asymptomatic, there can be a degree of bias if the control patients (non-COVID-19 group) become infected but exhibit an asymptomatic disease during follow-up. Nevertheless, potential patients fulfilling these characteristics can represent a minimal part of the sample size.

It is important to mention as strength of the study, that the events will be adjudicated by an independent committee blinded to the patients’ treatment allocation and trial results. This will guarantee a better evaluation of the study events.

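### The control group is defined by RT-PCR result alone in two places and by RT-PCR plus a garbled symptom condition in a third; one definition must be chosen

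*Protocol article*

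**What the plan says.** Four parts of the protocol article bear on who is compared with whom.

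- **Patient selection, group definitions.** The COVID-19 group is "patients with confirmed COVID-19 (positive RT-PCRT for SARS-CoV-2", with no symptom condition. The control group is "patients without COVID-19 (negative RT-PCR for SARS-CoV2, and absence of absence of suspicious symptoms".
- **Patient selection, entry criteria.** Apart from age, the inclusion criterion is "Patient who underwent a nasopharyngeal swab for real-time reverse transcriptase-polymerase chain reaction (RT-PCR) for SARS-CoV2 between March 2020 and August 2020". The only exclusion is "Those with terminal diseases and a life expectancy <1 year before the diagnosis will be excluded". Symptoms appear in neither criterion.
- **Abstract, Study and design.** The sample is "Consecutive patients older than 18 years, who underwent a real-time reverse transcriptase-polymerase chain reaction (RT-PCR) for SARS-CoV2", and "Patients will be classified into two groups, according to the results of the RT-PCR: COVID-19 positive or negative".
- **Statistical analysis plan.** The groups compared in the Cox model are "patients with positive vs. negative RT-PCR for SARS-CoV-2".

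Table 2 lists symptoms among the acute-phase data.

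**The concern.** The primary outcome, cardiovascular mortality at 1 year, is compared between two groups, and the document does not say consistently who is in the second one. Two people following different sections would assemble different control groups from the same records.

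The symptom condition is also one-sided. Positives enter whatever their symptoms, while negatives would be filtered. If the filter keeps only symptom-free negatives, a difference in outcome may reflect being ill at the time of the swab as well as being infected. The Discussion presents the control group as a means of reducing bias, so its definition matters to the main claim.

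A smaller defect sits beside this. The life-expectancy exclusion is timed relative to a diagnosis, and controls have none, so the rule has no stated reference date in that group.

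**Working it through.** The document states no sample size, event count or expected rate, so there is no figure of its own to reproduce. The check is a comparison of the definitions, followed by an illustration on assumed inputs.

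**Step 1. Where each eligible patient falls.** Every adult swabbed in the window and not terminally ill is eligible. Cross-classifying by swab result and symptoms:

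| Patient | RT-PCR only (Abstract, Statistical analysis plan) | Patient selection, read as no symptoms | Patient selection, read literally |
|---|---|---|---|
| Positive, symptoms | COVID-19 | COVID-19 | COVID-19 |
| Positive, no symptoms | COVID-19 | COVID-19 | COVID-19 |
| Negative, symptoms | Control | Neither group | Control |
| Negative, no symptoms | Control | Control | Neither group |

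The first column assigns everyone. Each of the other two leaves one class of eligible negatives unassigned, which conflicts with consecutive inclusion of tested patients. Deleting one of the doubled words moves the text from the last column to the middle one. It does not reach the first.

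**Step 2. Whether the Cox model can compensate.** With symptom-free controls, the symptomatic stratum contains positives only. A symptom coefficient would then be estimated among positives alone, and the group coefficient would rest on symptom-free positives against symptom-free controls. No control informs the comparison for symptomatic positives.

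**Step 3. Whether the choice could matter numerically.** All inputs here are assumptions; none is in the document. Infection has no effect, and 1-year cardiovascular death depends only on symptoms at the swab.

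- Risk without symptoms (p0) and with symptoms (p1): 1% and 2%, 1% and 3%, or 2% and 4%.
- Share of positives with symptoms (s+): 60%, 80% or 90%.
- Share of negatives with symptoms (s−): 30%, 50% or 70%.

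Formulas:

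- Risk in positives = s+ × p1 + (1 − s+) × p0
- Risk in all negatives = s− × p1 + (1 − s−) × p0
- Risk in symptom-free controls = p0; in symptomatic controls = p1

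Worked case with p0 = 1%, p1 = 3%, s+ = 80%, s− = 50%:

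- Positives: 0.8 × 0.03 + 0.2 × 0.01 = 0.026
- All negatives: 0.5 × 0.03 + 0.5 × 0.01 = 0.020
- Risk ratios: 0.026/0.020 = 1.30 (all negatives); 0.026/0.010 = 2.60 (symptom-free); 0.026/0.030 = 0.87 (symptomatic)

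Across the 27 combinations:

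| Controls | Crude risk ratio when the true effect is nil |
|---|---|
| All negatives | 0.92 to 1.75 |
| Symptom-free negatives only | 1.60 to 2.80 |
| Symptomatic negatives only | 0.73 to 0.95 |

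Using all negatives does not make the crude contrast unbiased. It does leave symptomatic and symptom-free patients in both groups, so the imbalance can be examined.

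**The case against.** The strongest reply is that this is one detailed definition plus two shorthand descriptions. The doubled phrase is plainly a slip, nobody would require suspicious symptoms in a group labelled as free of COVID-19, and an abstract may leave out a qualifier. Restricting controls to symptom-free negatives is also a defensible way to keep false-negative infections out of the comparison group.

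Part of this stands. The literal reading is unlikely to be intended, and the symptom-free definition is not wrong in itself. But the analysis section names the compared groups without the symptom condition, the article gives no reason for the condition, and the entry criteria and the consecutive-sampling statement do not fit with it. This is a stated definition that conflicts with itself, not a detail left to a fuller document.

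A reader might infer more than the document supports:

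- **That the contrast would be symptomatic illness against screened people.** It would not be purely that. Positives enter on RT-PCR alone, so symptom-free positives are included.
- **That events which prompted a control's admission would be counted as outcomes, because Table 2 lists no reason for the swab.** The detailed case report form is in a supplementary file that is not shown, so absent fields or event-onset rules cannot be established. Non-fatal admissions are not the primary outcome, and the mechanism could affect both groups under any control definition.
- **That the Discussion's statement "our findings will be applicable to any COVID19 patient, regardless of the severity of the disease" is contradicted.** It rests on consecutive inclusion of COVID-19 patients, which the control definition does not touch. The conflict over consecutive sampling is with the Abstract only.
- **That symptom adjustment should be the primary analysis.** Symptoms are partly a consequence of infection, so adjusting for them could remove part of the effect of interest.

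**Conclusion.** The concern holds in a limited form. The control group for the primary comparison is defined inconsistently, and correcting the doubled phrase does not resolve it. The loss of consecutive sampling and the partial confounding of infection with symptomatic presentation follow only if the symptom condition is applied, and the sampling problem concerns the controls only. Neither is established for the RT-PCR-only definition.

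The size cannot be read from the document. The ranges in the working show that the choice of definition can change the magnitude of the crude contrast, and its direction if the literal wording were followed. They rest on assumed risks and symptom shares and on no effect of infection. They are not a forecast of this registry's result. The missing reference date for the life-expectancy exclusion in controls is a minor, separate wording defect.

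**What to change.** 1. Correct the doubled phrase and use a single control definition in the Abstract, Patient selection and the Statistical analysis plan.
2. Preferably, keep all RT-PCR-negative patients as controls, set group by the qualifying swab, and report the contrast with symptom-free controls as a sensitivity analysis, using the symptom data already listed in Table 2.
3. If the symptom-free definition stays primary, stop describing the controls as consecutive, report how many negatives were left out, and run the all-negatives contrast as the sensitivity analysis.
4. Anchor the life-expectancy exclusion to the swab date in both groups.

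The cost is mainly wording and one extra analysis. Keeping all negatives has a drawback: some symptomatic negatives may be false negatives, which would dilute the contrast. The symptom-free sensitivity analysis addresses this. If centres have already left symptomatic negatives out of the database, the preferred option would require going back to the records. The alternative in item 3 then needs at least a count of those omitted, and its sensitivity analysis would need their data.

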### Data capture

Study data will be collected and managed using REDCap electronic data capture tools hosted at Hospital Clínic of Barcelona (redcap.clinic.cat). REDCap (Research Electronic Data Capture) is a secure, web-based software platform designed to support data capture for research studies, providing 1) an intuitive interface for validated data capture; 2) audit trails for tracking data manipulation and export procedures; 3) automated export procedures for seamless data downloads to common statistical packages; and 4) procedures for data integration and interoperability with external sources.

An anonymized and predefined electronic Case Report Form (eCRF) developed by the investigators will be filled by each participating center. The selected variables are oriented to the cardiovascular risk factors, conditions, medications, and outcomes (**Table 2**). Moreover, based on the current scientific literature, specific COVID-19 variable and treatment will be also collected. Charlson Comorbidity Index (CCI) will be used to assess patient’s comorbidities. CCI is a validated index for predicting life expectancy at ten years, depending on the age at which it is evaluated, and on the subject’s comorbidities [14]. The detailed eCRF format can be seen in the **S2 File**.

**Table 2 pone.0255263.t002:** Data to be obtained in the timeline of the study.

Baseline characteristics	Acute phase	Long-term (until 1 year)
Demographic data • Age • Sex Risk factors and baseline comorbidities • Hypertension • Diabetes mellitus • Hypercholesterolemia • Smoking status • Kidney chronic disease • Previous ACS • Previous Stroke • Heart failure • Atrial fibrillation • Previous PE and DVT • Cancer • Organ transplant • Immunosupresion • Frailty Charlson Comorbidity Index Baseline medication • Anti-hypertensive drugs and cardiovascular medication • Chronic anticoagulation • Oral hypoglycemic agents • Insulin • Proton pump inhibitors • NSAIDs	Symptoms Hospitalization • Length of stay Drugs: • Anti-hypertensive drugs and cardiovascular medication. • Anticoagulation • Antivirals • Immunosuppressive drugs • Vasopressors • ICU admission • Invasive mechanical ventilation Biomarkers • Hemoglobin* • Lymphocytes* • Platelets* • Creatinine** • HscTnI** • NT-proBNP** • D-dimer** • Fibrinogen* • Prothrombin time** In-hospital events: • All-cause death • Cardiovascular death • ACS • Stroke • DVT and PE • Cardiac arrhytmias • Bleeding • Red blood cell transfusion Discharge medication	New SARS-CoV-2 infection Vaccination against SARS-CoV-2 Outcomes • All cause death • Cardiovascular death • ACS • Stroke • Heart failure hospitalization • PE • Cardiac arrhytmias

ACS, acute coronary syndrome; DVT, deep venous thrombosis; Hs-cTnI, high sensitivity cardiac troponin I; NSAIDs, non-steroidal anti-inflammatory drugs; PE, pulmonary embolism.

*Lowest values during hospitalization.

*Highest values during hospitalization.

All the data will be obtained from electronic records (medical history). If deemed necessary, the investigator may check the patient vital status in the social national security database.

Clinical follow-up will be performed at 1-year. The flowchart and study timeline are detailed in **Fig 1**.

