## Conclusion

The results of the CV COVID-19 registry will contribute to a better understanding of the short and long-term implications of this disease. It will provide information about cardiovascular mortality and cardiac events at one year of follow-up. Also, it will identify characteristics associated with higher incidence of complications, defining a profile of COVID-19 patients with worse prognosis.

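### Acute-phase events, and major bleeding as printed, are captured only during each patient's own hospital stay, so a short-term group comparison would mix infection with admission and length of stay

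*Protocol article*

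**What the plan says.** - **Acute-phase capture** (Data capture, Table 2). The events in the acute column are "In-hospital events: • All-cause death • Cardiovascular death • ACS • Stroke • DVT and PE", then arrhythmias, bleeding and red-cell transfusion. The same column records "Symptoms Hospitalization • Length of stay" for each patient. No fixed number of days is given.
- **Long-term capture** (same table). The column running to 1 year lists all-cause and cardiovascular death, ACS, stroke, heart failure hospitalization, PE and arrhythmias. Bleeding is not in it.
- **Entry** (Patient selection). An adult qualifies as a "Patient who underwent a nasopharyngeal swab for real-time reverse transcriptase-polymerase chain reaction (RT-PCR) for SARS-CoV2" in the inclusion period. Admission is not required. The Discussion says that "our findings will be applicable to any COVID19 patient, regardless of the severity of the disease".
- **Controls** (Patient selection). They are defined by "negative RT-PCR for SARS-CoV2, and absence of absence of suspicious symptoms". The wording is garbled but apparently means symptom-free.
- **Outcomes** (Outcomes and definitions). Major bleeding, BARC type 3 or higher, is among the secondary outcomes.
- **Analysis** (Statistical analysis plan). "Differences in proportions will be tested with Chi-square test or Fishers exact test". For follow-up, "Kaplan-Meier method will be used to derive the event rates at follow-up and to plot time-to-event curves", with a Cox model for cardiovascular death.
- **Claim** (Conclusion). The registry "will contribute to a better understanding of the short and long-term implications of this disease".

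**The concern.** The in-hospital events are the only short-term event data in Table 2, and they are observed for as long as each patient happens to be in hospital. Length of stay varies between patients and can itself be changed by infection. Patients who were swabbed but never admitted contribute no acute observation. Controls were probably tested and admitted for other reasons than cases, so nothing ensures that admission shares and stays are alike in the two groups.

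A chi-square or Fisher test on such proportions takes no account of time at risk. The group observed for longer accumulates more events even when the daily risk is the same. At stake are any short-term contrast reported between RT-PCR positive and negative patients, and the one declared secondary outcome whose printed capture stops at discharge.

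**Working it through.** The article gives no stay length, admission share, event rate or sample size, so there is no figure of the plan to reproduce. All numbers below are assumed and serve only as illustration.

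**Inputs.** From the article: two groups and a two-sided test at 0.05. Assumed: a constant daily hazard h that is the same in both groups (no effect of infection), admitted share a, and stay L in days.

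**Formula.** In-hospital proportion p = a × (1 − exp(−h × L)).

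**Step 1: everyone admitted, 12 against 4 days, h = 0.001.**
- 12 days: 1 − exp(−0.012) = 1.19%
- 4 days: 1 − exp(−0.004) = 0.40%
- Ratio about 3.0, with no true effect.
- With 1000 per group: difference 0.0119 − 0.0040 = 0.0079; standard error √[(0.0119 × 0.9881 + 0.0040 × 0.9960)/1000] = 0.0040; z about 2.0. The chance of p < 0.05 is then about Φ(2.0 − 1.96) ≈ 0.52. Simulation with exponentially distributed stays gave 51 to 52%.

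**Step 2: sensitivity to stay and group sizes** (simulated, h = 0.001, chance of p < 0.05).

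| Mean stays (days) | 1000/1000 | 2000/500 | 3000/1000 |
|---|---|---|---|
| 12 vs 4 | 52% | 29% | 64% |
| 8 vs 4 | 17% | 7% | 21% |

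A repeat of the 8 vs 4 case at 1000/1000 gave 19%. Equal stays gave about 5%.

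**Step 3: unequal admission as well** (formula above, h = 0.001).

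| Cases | Controls | p cases | p controls | Ratio | P(p < 0.05), 1000 per group | P(p < 0.05), 2500 per group |
|---|---|---|---|---|---|---|
| 70%, 10 d | 70%, 10 d | 0.70% | 0.70% | 1.0 | 5% | 5% |
| 70%, 10 d | 70%, 5 d | 0.70% | 0.35% | 2.0 | 19% | 40% |
| 70%, 12 d | 30%, 5 d | 0.84% | 0.15% | 5.6 | 59% | 93% |
| 90%, 14 d | 10%, 3 d | 1.25% | 0.03% | 42 | 93% | 100% |

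Over h = 0.0005 to 0.002 the ratios hardly move. For the third row, the chance of a significant result at 1000 per group runs from 34% to 87%. The last row is an extreme, and its control count (0.3 expected events per 1000) is too small for the normal approximation to be exact. Exchanging the two groups' stays and admission shares inverts every ratio, so the direction depends on inputs that the article does not give.

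**Step 4: a common window.** With 30 days from the swab for every patient, p = 1 − exp(−30h) in both groups: 1.49%, 2.96% and 5.82% at h = 0.0005, 0.001 and 0.002. The ratio is 1.0 and the error rate returns to about 5%.

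**Step 5: which declared outcomes are caught.** Setting Outcomes and definitions against Table 2, infarction (as ACS), stroke, heart failure hospitalization, PE and arrhythmias all appear in the long-term column. Major bleeding does not; it appears only among in-hospital events. With an assumed 12-day stay, bleeding would be observed for 12/365 = 3.3% of the year; with 4 days, 1.1%; with no admission, not at all.

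**The case against.** The strongest reply is that no such comparison is planned. The chi-square sentence sits beside the t-test as a generic rule for descriptive variables. For events the plan names Kaplan-Meier and Cox, and the Abstract's statement that outcomes will be compared follows a list of 1-year outcomes. Table 2 is a data-capture list and defines no endpoint. The short-term claim is one phrase in the Conclusion, and the next sentence speaks of one-year results. The eCRF (S2 File) and Fig 1 are not shown and may define a window.

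Much of this stands. A group test of in-hospital proportions is implied by the two-group design and the short-term claim, but it is not stated. Three stronger readings are tempting and are not supported:

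- **That a short-term difference would reflect time at risk and not infection.** It would reflect both, and a longer stay may itself result from infection.
- **That the bias favours more events in the positives.** This is plausible, but the article gives no stays or admission shares for either group.
- **That the 1-year results or post-discharge rates are distorted.** No post-discharge analysis is specified. Deaths, ACS, stroke, PE and arrhythmias stand in both columns, which fits cumulative counting to 1 year.

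The reply does not cover bleeding. It is a declared secondary outcome, and its printed capture ends with the stay. The Abstract's list of 1-year secondary outcomes omits it, so nothing in the article supplies another window.

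**Conclusion.** The point holds in a limited form. As printed, the acute-phase window is patient-specific and empty for those never admitted, so comparing these proportions between groups by chi-square or Fisher would confound infection with admission and stay. The distortion could be nil (equal admission and stay) or several-fold: ratios of about 2 to 6 in the moderate assumed scenarios. Every magnitude rests on assumed stays, admission shares and an equal constant hazard. Major bleeding is affected directly, unless the eCRF collects it after discharge. The primary outcome and the other 1-year outcomes are not affected, provided all events are counted by date from the swab. This is a cheap improvement worth making, not a flaw in the main analysis.

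**What to change.** 1. For any short-term comparison between groups, define one fixed interval from the index swab date (for example 30 days) for all patients, admitted or not. Assign events by date and report cumulative incidence with the time-to-event method already planned.
2. Add bleeding to the long-term column of Table 2, so that it is counted to 1 year like the other secondary outcomes.
3. Keep in-hospital events as a description of admitted patients only, and say so.

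The cost is one added definition, plus some record review for bleeding after discharge and for early events in patients who were not admitted. Event dates are already needed for Kaplan-Meier and Cox, and the data come from electronic records.
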